## 5 Patient and Public Involvement (PPI)

### 5.1 *Past PPI*

Patient and public involvement has been key to the development of this proposal. In one-to-one interviews with three parental caregivers of people with psychosis and one focus group of four attendees of the Carers Centre in Brighton, caregivers identified three needs that writing interventions can address: a) the limited opportunities to express themselves; b) the limitations of support groups to provide peer support because caregivers are already overburdened with their own responsibilities; and c) the limited availability and ability to physically attend meetings. This feedback has been vital in us defining the rationale for this research study.

We also consulted the focus group of carers on the study design, materials, and intervention. Specifically, they helped us consider alternative approaches to recruitment (e.g. third sector organisations), the outcome measures that are meaningful to carers (e.g. wellbeing measures), and most significantly the content of the control conditions (e.g. the image used in the WC group). From these discussions, we added a ‘no writing’ arm to the trial as carers felt that it might be the act of writing, rather than the content, that is beneficial; they perceived the writing task as offering caregivers an invaluable space where they could focus upon their own needs, rather than the needs of their loved one. All of the study materials were checked by caregivers to ensure that they were clear, accessible, and easily understood.

### 5.2 *Future PPI*

A Lived Experience Advisory Panel (LEAP) will continue to be involved in the study until its end. The LEAP will be made of people whom either have previous experience of or are currently a carer for someone with a mental health problem. The group will meet at least three time points during the study with members of the research team to discuss the progress of the study (before ethics submission, after recruitment has started, and after data has been analysed). They will continue to advise on the recruitment and retention procedures (including the participant information sheet), and will consult on the plans for dissemination to participants following data analysis. The LEAP will also assist with the analysis of the qualitative data; once themes are established, they will be invited to look at the themes with supporting excerpts and assess their face validity.

## 6 Methods/Design

### 6.1 *Type of study*

External pilot randomised controlled trial (RCT) with three parallel arms.

## 6.2 *Participants*

Potential participants will be screened according to the inclusion and exclusion criteria detailed below, using an eligibility assessment (see appendix). All participants will have caring responsibilities for a person with psychosis. Because of the nature of the intervention (PWD), all participants must be able to read, write and communicate in English. This study will only be recruiting carers aged 50 or over.

### 6.2.1 Inclusion/exclusion criteria

#### **Inclusion Criteria:**

All participants must meet the following criteria:

- Classified as a primary caregiver as defined by the Royal College of General Practitioners (2011, p. 9): “any person who provides unpaid support to a partner, child, relative or friend who couldn’t manage to live independently or whose health or wellbeing would deteriorate without this help.”
- Aged 50 years or over
- Providing care for someone with a psychosis diagnosis - psychosis is defined here as including the following diagnoses:
  - Schizophrenia
  - Schizoaffective disorder
  - Schizotypal Personality Disorder
  - Delusional disorder
  - Psychosis not otherwise specified
  - Bipolar
  - Depression with psychotic features
- Able to read, write and communicate in English

#### **Exclusion Criteria:**

Participants will be excluded if:

- Currently receiving or have confirmed plans to engage in psychological therapy of any form (including family therapies)

## 6.3 *Aims & Objectives*

The overall aim of this study is to determine whether PWD improves the wellbeing of older adult caregivers of people with psychosis. The present pilot trial will determine whether the intervention shows promise (determined by between-group effect sizes), and consequently whether a definitive trial is justified. We will use quantitative methods to explore the following aims:

- a) To report the means and standard deviations separated by group allocation for all study time points
- b) To calculate the group (PWD vs WC vs NWC) x time (baseline vs 1 month/ 3 month/ 6 month) effect sizes and associated 95% confidence intervals for the primary outcome measure
- c) To estimate the study recruitment rates
- d) To estimate the study retention rates

We plan to use qualitative methods (exit interviews, and anonymous feedback forms) to explore the following aims:

- a) The acceptability of the conditions (PWD, WC and NWC)
- b) The subjective experience of the conditions
- c) The subjective experience of the research study
- d) What the next steps for the research programme should be

#### 6.4 *Recruitment and consent methods*

To recruit participants for this study we will employ a number of recruitment strategies. These recruitment strategies are: (1) through clinical services, (2) the research network, (3) via psychosis patients, (4) collaboration with third sector organisations, (5) promotional materials, (6) GP screening, (7) Sussex Partnership NHS Foundation Trust opt out scheme.

**Clinical Services:** Mental health clinicians working in the host site (Sussex Partnership NHS Foundation Trust) will be asked to identify any potential participants for this study. We will mostly be asking clinicians whom have clients with psychosis to pass on information about the study to their client's carer. The clinicians will be the first to approach the potential participant regarding this research study, and will be encouraged to pass on the study information to any potential participants. If the potential participant is interested in taking part in this study they can either contact the research team directly themselves, or the clinician can make a referral (once the potential participant has shown an interest).

**Research Network:** The Research Network is a database of patients, carers, and clinicians whom have given their permission to be contacted about research studies by the Research and Development at Sussex Partnership Trust. All members of the Research Network who match the inclusion criteria for the study will be sent information about the study by the R&D Department. Interested potential participants will be able to contact either the R&D Department or the research team directly and enquire about the study.

**Via psychosis patients:** Where Sussex Partnership NHS Foundation Trust mental health services with a psychosis diagnosis are involved in research studies and clinics, they will be asked if they have a caregiver. Where patients respond 'yes', they will be given the promotional materials from this study. These patients will be asked to pass on the promotional materials to their caregiver – the promotional materials will only be given to patients that given their permission to be contacted about research studies. The promotional materials will contain information on how the caregiver can find out more about the study and get involved. The research team will not make direct contact with these patients. Contact will only be made by research staff (e.g. Clinical Research Coordinators) or research clinicians who have consent to contact the patients in reference to research studies.

**Third Sector Organisations:** The study will be advertised through third sector organisations that are likely to support eligible participants i.e. carers charities, and/or mental health charities. Contact will be made with third sector organisations to

promote the study. Where possible members of the research team will attend third sector events and/or meetings to promote the study. If potential participants are then interested in taking part in the study they can either contact the research team directly or a referral can be made by a third sector worker.

**Promotional Materials:** Study promotional materials (i.e. posters and flyers) will be displayed in appropriate venues across Sussex. Study posters will be displayed in GP surgeries, mental health facilities, and appropriate third sector facilities. All of the promotional material will contain information on how to contact the research team if the potential participant is interested in taking part.

**GP screening:** General Practices in East and West Sussex will search their caregivers register/database and electronic patient records for caregivers using Read codes. Also the appointed 'carer's carer' within each practice will be asked to identify potential participants. The research team will also seek permission to attend Carer's Support events to promote the study. Identified caregivers will be sent information about the study by either the GP or a Clinical Research Coordinator (CRC); or they can self-refer. Interested potential participants will be able to contact either the CRC or the research team directly and enquire about the study.

**Opt Out System:** Sussex Partnership NHS Foundation Trust have an opt out scheme in place for consent to contact about research. Members of the Research & Development Department will contact patients, who have not opted out of being approached about research, to discuss the study and invite their carer (if eligible) to take part. Only patients who have not opted out of being contacted about research will have identifiable personal information reviewed by members of the Trust's Research & Development Department. They will initially be contacted by members of the Research and Development Department by letter. If the carer of this patient is interested in the study they can either contact a member of the Research and Development Department or contact the research team directly for further information. To clarify, the opt out system will be used to identify those patients with a psychosis diagnosis who have not opted out of being approached about research. The initial letter will make it clear that the research team would like them to pass the study information onto their carer wherever possible.

Irrespective of the method used to recruit participants, the research team will not personally contact any potential participants without their verbal consent to do so. The initial contact with the research team will either be initiated by the potential participant themselves (self-referral), via a clinician referral, third sector referral, or via contact with a CRC. The research team will not access patient or GP records to identify participants. Copies of the PIS will be given to potential referrers to pass onto the potential participants. During the first interaction between the potential participant and the research team, if the potential participant has not already received a copy, they will be given a copy of the PIS. They will be asked to read through the information, discuss the study with friends and/or family, and formulate any questions they may have about the study. After a 'cooling-off' period of 24 hours, the research team will contact the potential participant again to see if they would like to take part in the study.

If the potential participant is still interested in taking part in the study, they will be invited to attend an initial meeting. This initial meeting can take place at the potential participants home or a convenient clinical setting (e.g. GP surgery, mental health building). During this first meeting, a member of the research team will discuss the study with the potential participant and answer any questions they may have. If a participant decides to take part they will be asked to complete an eligibility assessment – this will establish whether the participant meets the study entry criteria. If the participant is eligible and they would still like to take part in the study, then they will be asked to sign two copies of a consent form: one copy will be kept by the research team, and the other copy will be for the participant to keep. For participants who choose not to consent they will exit the study at this point. During this meeting, the participant will be asked to also complete the baseline assessment. The baseline assessment is comprised of multiple questionnaires that will be used as the study outcome measures.

For participants that are not eligible to take part they will be told so immediately following the eligibility assessment. These individuals will be informed why they are not eligible for the study. The reason for their ineligibility will be framed in a positive way so as to minimise disappointment. These individuals will also be offered the opportunity to join the Research Network (if they are not already members). Joining the Research Network will mean they will be sent invitations to participate in other research studies which may be more appropriate, as well as invitations to research and development events. Their referrer (for those that did not self-refer) will also be informed that they are not suitable to take part.

To clarify the recruitment and consent process will proceed as follows:

[figure not shown]

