#### 4.1 *Research question*

This is a pilot study that aims to answer a number of feasibility questions that will determine whether a definitive trial is justified, and if so the design of this trial. Specifically this pilot trial aims to answer the following questions:

- a) Are carers of people with psychosis willing to be recruited and randomised?
- b) Are there retention issues? If yes, at what stages did these occur? What were the reasons?
- c) Are follow-up data complete i.e. no more than 33% attrition?
- d) Can the positive written disclosure (PWD) be delivered with sufficient fidelity?
- e) Is there sufficient evidence for scaling up to a definitive randomised controlled trial?
- f) What sample size is needed to power a full scale randomised controlled trial?
- g) Are there any safety issues or adverse events related to the completion of writing tasks?
- h) What did the carers think of the intervention and study design?

The research question for the definitive trial will be: Does positive written disclosure (PWD) improve both the psychological and physical wellbeing of older adult carers of

people with psychosis compared to a writing (WC) and non-writing control (NWC) condition?

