### 7.12 Data sharing

Data may be shared outside of the research team as part of future research studies. Only anonymised data will be shared. This will be made explicit to participants on the study consent form. The participant's personal details will not be shared with anyone outside of the research team. In addition the number of participants recruited, and how they are recruited will need to be recorded and shared with both the Sussex Partnership NHS Foundation Trust research and development department and the National Institute for Health Research. The number of participants recruited will need to be shared to inform recruitment targets for both institutions. None of the personal details of the participants will be shared.

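### Eligibility is assessed only after a carer provisionally agrees to take part, so early decliners have unknown eligibility and uptake among assessed carers overstates willingness

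*Protocol*

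**What the plan says.** The first feasibility question in section 4.1 is "Are carers of people with psychosis willing to be recruited and randomised", and aim (c) in section 6.3 is "To estimate the study recruitment rates". Neither gives a denominator or a threshold.

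Section 6.4 fixes the order of steps:

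1. Clinicians, GP practices, the R&D Department, third sector workers or the patient pass on the study information, and "the research team will not personally contact any potential participants without their verbal consent to do so". The team does not look at patient or GP records.
2. At first contact the carer receives the information sheet, if they do not already have it.
3. After 24 hours, "the research team will contact the potential participant again to see if they would like to take part in the study".
4. "If the potential participant is still interested in taking part in the study, they will be invited to attend an initial meeting".
5. At the meeting the study is discussed. Then: "If a participant decides to take part they will be asked to complete an eligibility assessment".
6. "If the participant is eligible and they would still like to take part in the study, then they will be asked to sign" the consent form. Those who do not consent leave here.

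Section 7.2 lists the eligibility assessment as six items. Section 7.3 sets the recruitment target at 60. Section 11 puts randomisation in week 2, after consent and baseline in week 1. Section 7.12 states that "the number of participants recruited, and how they are recruited will need to be recorded" and shared with the Trust's R&D department and the national research funder.

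**The concern.** Willingness is a share of eligible people. To estimate it, each person who says no must be classed as eligible or not. The order in section 6.4 lets carers say no twice before anyone asks the eligibility questions: at the call in step 3, and at the meeting before the form in step 5. The team cannot fill the gap afterwards, because it does not consult records, and an analysis plan cannot recover an answer that was never collected.

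Section 4.1 says these questions determine whether a definitive trial is justified and how it is designed. If the rate carried forward is conditional on having already agreed in principle, a high figure could come from a population in which most eligible carers accept or from one in which most refuse. The number of carers to approach, and the time needed to recruit them, would then be set too low.

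**Working it through.** The plan states no recruitment rate, so there is no figure to reproduce. The check is of the order of steps, followed by an illustration of how the bias behaves.

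**Who can be classified, by exit point (section 6.4)**

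| Exit point | Refusal visible to the team? | Eligibility known? |
|---|---|---|
| No reply to an invitation | No | Not to the team |
| No at the call after 24 hours | Yes | No |
| No at the meeting, before the form | Yes | No |
| No after the form, at consent | Yes | Yes |
| Withdrawal around randomisation | Yes | Yes |

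The second and third rows are the problem. The last two rows show that some eligible decliners can be identified.

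**Direction and form of the bias**

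Let C be the number recruited, A the eligible carers who decline after the form, B the carers in contact who decline before it, and q the share of B who are eligible.

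- Uptake among assessed eligible carers: M = C / (C + A)
- Uptake among all eligible carers in contact: T = C / (C + A + qB)
- Ratio: M / T = 1 + qB / (C + A)

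The ratio exceeds 1 whenever any early decliner is eligible, so M can only overstate T. M equals 100% only if A = 0.

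**Illustration**

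C = 60 is the target in section 7.3. A, B and q are assumptions; the documents give none of them.

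| A | M | T if B = 30, q = 0.5 | T if B = 120, q = 1.0 |
|---|---|---|---|
| 0 | 60/60 = 1.00 | 60/75 = 0.80 | 60/180 = 0.33 |
| 5 | 60/65 = 0.92 | 60/80 = 0.75 | 60/185 = 0.32 |
| 10 | 60/70 = 0.86 | 60/85 = 0.71 | 60/190 = 0.32 |

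For A = 0 the ratio M / T runs from 1 + 15/60 = 1.25 to 1 + 120/60 = 3.00. Measured uptake moves between 0.86 and 1.00 with A and does not respond to B at all. Uptake among all eligible carers in contact moves from 0.80 to 0.32 over the same grid.

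**The case against.** A reader might infer that eligible decliners can never be identified, so that question (a) is answered yes by construction. The documents do not support that, for four reasons:

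- Section 6.4 sets a second decision after eligibility is known, and eligible carers who decline consent leave there as an identifiable group.
- Recruitment can fall short of 60, which would itself be an unfavourable answer.
- Refusals at the call are made to the research team and can be counted, even with eligibility unknown.
- Section 9 allows withdrawal at any point, and randomisation comes a week after consent, so reluctance to be randomised can show itself.

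The protocol also does not define the recruitment rate as randomised over assessed-eligible. It could mean recruits per month or per route. Section 7.12 cannot be read as proof that refusals go unrecorded, because it covers what is shared with outside bodies. The recruitment flow chart and the CONSORT diagram are not shown and may count people approached or declining. On the Research Network route, the R&D Department writes to members who match the inclusion criteria, so non-responders there are partly classified, though not on the therapy exclusion.

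All of this stands, and it removes any claim of a predetermined result. It also means that the lack of a refusal log or a stated denominator would, alone, be only missing detail. It does not remove the ordering problem: no flow chart or later analysis can supply the eligibility of carers who left before the questions were put.

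A further fair objection is that asking sooner collects answers about the carer's therapy and the cared-for person's diagnosis from people who may not join. That trade-off is real, and it is why verbal agreement belongs in the fix.

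**Conclusion.** The concern holds in limited form. Under section 6.4, carers who decline at the call or at the meeting before the form have unknown eligibility, so uptake calculated among assessed-eligible carers is biased upward as an answer to question 4.1(a) and aim 6.3(c). The direction follows from the order of steps, provided at least one early decliner is eligible. The size cannot be estimated from the documents. The figures above (measured 86% to 100% against 80% down to 32%) rest on assumed refusal counts and show only that the gap could be large; they do not forecast it. The plan should be changed before recruitment starts, because the information is lost once a carer has left. The point does not invalidate the pilot or its other aims.

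**What to change.** In section 6.4, offer the six eligibility questions, with the carer's verbal agreement, at first contact with the research team or at the latest at the cooling-off call, before asking whether the carer will take part. The form already precedes signed consent, so this moves an existing step forward. Then:

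- Count refusals by stage (call, meeting, consent, randomisation), with an optional reason.
- Report aim 6.3(c) as randomised / eligible carers who made contact. Bound it by treating contacts of unknown eligibility as all eligible and then as none eligible. For example, 60 randomised, 5 known eligible decliners and 30 of unknown eligibility would give 60/95 = 63% to 60/65 = 92% (the 5 and 30 are assumed).
- For mailed routes, also report randomised / invitations sent, where the sender can supply the count.

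The cost is revised protocol wording, a simple log, and a few minutes of questions to some carers who will not join. The stated rate will look less favourable. Eligibility stays unknown for people who never make contact, and the change does not solve that. No extra participants are needed.

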### 6.5 Assessment process

| Assessment                   | Carried out by | What the assessment is for                                  | How is the assessment carried out            | At what stage is the assessment carried out |
|------------------------------|----------------|-------------------------------------------------------------|----------------------------------------------|---------------------------------------------|
| Baseline Assessment          | RF or RA       | Measure outcomes before randomisation                       | In person
Online or paper based           | After consent                               |
| 1 month assessment           | P              | Measure outcomes post intervention                          | Via post
Online or paper based            | 4 weeks post randomisation                  |
| 3 month follow up assessment | P              | Measure outcomes at short term follow up time point         | Via post
Online or paper based            | 12 weeks post randomisation                 |
| 6 month follow up assessment | P              | Measure outcomes at long term follow up time point          | Via post
Online or paper based            | 24 weeks post randomisation                 |
| Exit interview               | RF or RA       | Generate qualitative data on participants experience of PWD | In person or via telephone
Audio recorded |                                             |

RF= Research Fellow

RA= Research Assistant  
P= participant

The assessment will take place in either the participants own home or in a convenient NHS building (e.g. GP surgery or mental health building). Where assessments are carried out in the participant's home, the lone working policy will be followed (see section 9 – ethical considerations). The assessments at the 1, 3 and 6 month time points will not require any direct contact with the research team. The participants will be sent the assessment pack in the post with a covering letter. They will be asked to complete the questionnaires and return them in a pre-post envelope. Participants will also have the option to complete all assessments online (except for the exit interview).

